## Study Title

Prevention and rehabilitation after acute coronary syndrome: new strategy trough telemonitoring.

## Protocol Code

TSB2014

## Centres where the study is planned to be carried out

Hospital Universitario Arnau de Vilanova. Valencia.

## CEICs that evaluate it

Hospital Universitario Arnau de Vilanova, Valencia.

## General Objective

To demonstrate that a telerehabilitation program improves physical activity compliance at 10 months follow-up, relative to a conventional rehabilitation program.

## Secondary Objectives

Very the improvement of the following parameters, after the intervention:

- Demonstrate an increase in oxygen consumption (VO2max).

- Demonstrate increased exertion time.

- Demonstrate an increase in workload.

- Decrease the presence of symptoms.

- Obtain improvement in lipid profile

- Decrease in ultrasensitive C Reactive Protein (CRPus)EQ

- Demonstrate increased adherence to the Mediterranean diet.

- Demonstrate improved results in psychological state.

- Demonstrate increased willingness to quit smoking and smoking cessation.

- Demonstrate a decrease in the sedentary lifestyle indicator.

- Improved measurement of carotid-femoral pulse wave velocity.

- To evaluate the cost per patient/month in the control cases of conventional rehabilitation and extended tele-rehabilitation intervention.

- To evaluate the time to return to work.

## Design

Randomised, controlled, clinical trial with two arms (cardiac tele-rehabilitation group and conventional in-hospital rehabilitation group).

## Disease or disorder under study

Acute Coronary Syndrome

## Drug Data

Does not apply.

## Population under study and total number of subjects

The study population consists of men and women with a maximum age of 72 years diagnosed with acute coronary syndrome who will be enrolled in a cardiac rehabilitation program. Sixty patients will be included in two groups of 30 subjects assigned to each rehabilitation program.

## Inclusion Criteria

- Patients after uncomplicated acute coronary syndrome of both sexes.

- Completion of a maximal or symptom-limited exercise test without angina or electrical ischaemia.

- Age 72 years or less.

## Exclusion Criteria

- Refusal of informed consent

- At the discretion of the investigator, primarily due to advanced biological age.

- Severe renal insufficiency (GFR < 30ml/min/1.73 m2).

- EF less than 50%.

- Hepatic insufficiency GOT >2 times normal value.

- Uncontrolled blood pressure (>140/90 mmHg).

- Uncontrolled heart failure.

- Dissecting aortic aneurysm.

- Uncontrolled ventricular tachycardia or other dangerous ventricular arrhythmias (multifocal ventricular activity).

- Aortic or mitral valve disease.

- Recent systemic or pulmonary embolism.

- Active or recent thrombophlebitis.

- Acute infectious diseases.

- Uncontrolled supraventricular arrhythmias or tachycardias.

- Repeated or frequent ventricular ectopic activity.

- Moderate pulmonary hypertension.

- Ventricular aneurysm

- Uncontrolled diabetes, thyrotoxicosis, myxoedema

- Hepatic or renal insufficiency and other metabolic insufficiencies.

- Conduction disorders such as: Complete AV block. Left bundle branch block. Wolf-Parkinson-White syndrome.

- Fixed rate pacemaker.

- Severe anaemia.

- Psychoneurotic disorders.

- Neuromuscular, musculoskeletal and arthritic disorders that may limit activity.

## Data Analysis

The primary efficacy variable is METs-minutes/week. For the calculation of the power of the study, a 12% possible loss to follow-up was estimated. Thus, accepting an alpha risk of 0.05 in a bilateral test with 27 subjects in the control group and 27 patients in the intervention group, the power of the hypothesis test is 95% to detect as statistically significant the difference between the mean of 5000 in the first group and the mean of 4000 in the second group after rehabilitation. Based on the potential impact of the telerehabilitation intervention on compliance with the physical activity recommendation at 6-month follow-up and considering METs-minutes/week as the unit of measurement, it has been estimated that patients in the intervention group will achieve 5000 METs-minutes/week while in the conventional rehabilitation group they will achieve 4000 METs-minutes/week.

The characteristics of the patients in the two study groups will be described (applying the appropriate estimators according to the type of variables, such as means and confidence intervals, medians and interquartile ranges or proportions) and possible differences between the groups will be assessed using appropriate statistical tests of differences of means, distributions of ranks or proportions. The comparison of the primary variable and the secondary variables of the study in both groups at baseline, at four months and 10 months after the start of rehabilitation will be carried out using Pearson χ2 test for qualitative variables (Fisher exact test for dichotomous variable) or Student t-test for independent samples for quantitative variables (Mann-Whitney U test when parametric assumptions couldn’t be assumed). The treatment effects within groups (at four months or ten months) will be assessed using McNemar-Bowker test of symmetry for qualitative variables (McNemar test for dichotomous variable) or Student t-test for paired samples for quantitative variables (Wilcoxon signed-rank test when parametric assumptions couldn’t be assumed). The relationship between quantitative variables will be assessed by Pearson’s correlation coefficient (Spearman’s rank correlation coefficient when parametric assumptions couldn’t be assumed). Multiple linear regression models will be used to assess the significance and magnitude of the intervention effect controlling for possible differences in patient characteristics between groups. In general, backward-forward models will be used, initially constructing the complete models and excluding non-significant variables one at a time (p for variable removal: 0.10) but trying to include the previously removed variables after each exclusion (p for incorporation: 0.05. The analysis will be performed on an intention-to-treat basis. For the economic evaluation, the unit cost will be obtained by quantifying the consumption of resources and applying the official cost rates of the Valencian Health Agency or, if these are not available, they will be estimated by assessing the time and cost of the resources involved. Two-sided exact p-values will be calculated whenever possible and p-values ≤ 0.05 were considered statistically significant. Data will be analysed using IBM SPSS Statistics 22 and R 4.0.2 for Microsoft Windows.

## Calendar

Start of study: 01-10-2018

End of recruitment: 01-02-2019

End of study: 01-02-2020

Final report: 01-04-2020

Publication: 01-06-2020

# Rationale for the study

Cardiac rehabilitation after myocardial infarction or coronary syndrome, whether or not followed by percutaneous or surgical revascularisation, continues to be recognised in the latest guidelines and recommendations published by the major scientific societies as a class I^1,2^. These programs were proposed by the World Health Organisation in the 1960s to improve the quality of life and prognosis of patients with heart disease. The cardiac rehabilitation includes, in addition to a physical training program, guidelines for healthy nutrition, psychological counselling and stress management. This, together with pharmacological treatment, constitutes the best clinical practice in cardiovascular prevention for our patients. Despite this evidence, the number of patients joining these programs in Europe is still less than 30%, a figure that is reduced in Spain to a symbolic 3%, according to data from the EUROASPIRE III study^3^. According to this study, 17% of those surveyed after a coronary event still smoked; 35% were obese; 56% had hypertension and 51% had dyslipidaemia. Considering that the measures carried out in these rehabilitation programs are very cost-effective in reducing cardiovascular risk, it is difficult to understand why they have not received greater impetus from health authorities and professionals involved so far. Instead, the impact of pharmacological prevention measures, enhanced in recent years, has contributed to drastically improve the prognosis of patients after acute coronary syndrome, partly diminishing the weight of evidence for the benefit of cardiac RHB programs^4,5^. In two of the latest prospective trials, cardiac BHR programs failed to demonstrate positive results on the primary endpoint (total mortality, myocardial infarction and hospital readmission), although they were superior on some secondary endpoints such as non-fatal infarction or length of hospital stay^6,7^. Taylor et al, in 2004 noted that the benefit of cardiac RHB with exercise alone was 16% in terms of cardiovascular mortality. If it was also incorporated into a comprehensive program, including risk factor control and educational measures, the benefit amounted to 24% ^8^. In a later published meta-analysis, the authors estimated that half of the 28% reduction in cardiac mortality achieved was attributable to the reduction in major risk factors and, therefore, there was no independent risk reduction due to physical exercise alone ^9^. Martin et al, in a prospective cohort study, showed that subjects (n=2900) who completed a full rehabilitation program had a lower risk of death, cardiac and overall hospitalisation compared to those subjects (n=554) who did not^10^. Suaya et al, in an analysis to control for a number of variables in participants and non-participants in BHR programs, among 60,000 coronary subjects over 65 years of age included in MEDICARE, observed a 21-34% reduction in 5-year mortality in BHR program users compared to non-users^11^. Unfortunately, in this multidisciplinary program the impact of physical exercise on mortality reduction was not specifically analysed. In any case, it seems that the benefit of physical exercise is inseparable from the other measures. Therefore, the European and American guidelines on cardiovascular prevention describe the recommendations for physical activity and participation in rehabilitation programs in separate sections. Moreover, the benefit of cardiac rehabilitation programs is directly related to the length of time the patient remains in the program. This relationship has been analysed in 3,161 patients with a recent coronary event included in the Medicare database, who attended at least one rehabilitation session. After 4 years of follow-up, patients who attended 36 sessions had a 14% lower risk of death and a 12% lower risk of myocardial infarction than those who attended 24 sessions; a 22% lower risk of death and a 23% lower risk of myocardial infarction than those who attended 12 sessions; and 47% lower risk of death and 31% lower risk of myocardial infarction than those who attended only one session. However, only 18% of patients completed the maximum of 36 sessions^12^. On the other hand, it appears that health-related quality of life does not differ in relation to the duration of the 6-month rehabilitation program compared to a 12-month rehabilitation program^13^. Current rehabilitation programs based on inpatient supervision have several limitations. One of the most important is the lack of adherence in the medium and long term. At the end of phase II, few patients adopt the advice given for the rest of their lives and continue to do physical activity at the required intensity (phase III). There is a direct relationship between the degree of physical training maintained and cardiovascular morbidity and mortality^14,15^ and therefore some of the benefits achieved are reversed over time. To overcome these limitations, modifications and new strategies to existing programs are probably required. Outpatient rehabilitation programs are being evaluated in recent years as alternative strategies with good results^16^. The development of telematic applications and Internet-based platforms constitute the fundamental tools for carrying out these home-based rehabilitation programs^17^. There are some experiences in which their feasibility has been demonstrated, increasing adherence to physical activity^18^. Their use in conditions of distance from the hospital and their equal or lower cost in some cases are other possible advantages^19^ . The present study is aimed at validating a new Integrated Telerehabilitation System as support for post-infarction rehabilitation, optimising it and testing its usefulness in terms of improving adherence to physical exercise and cardiovascular risk parameters. It should also be analysed whether there are limitations to the use of these technologies by older people with no previous experience in the use of new communication technologies. The economic analysis will make it possible to estimate whether there are added advantages such as cost containment. The importance of these innovations has led the European Union to allocate funds within the Seventh Framework Program to promote new technological developments. The platform and application used in this trial, with the appropriate modifications, are already being used in the follow-up of heart transplant patients ^20^. In a context of rising health system costs, it is important to raise patient awareness of the responsibility of maintaining health by adopting healthier lifestyle habits. Moreover, these innovations in rehabilitation programs can encourage motivation and act synergistically, together with other pharmacological measures, to achieve the prevention objectives that require so much work and effort on the part of all the actors involved.

# Objectives

## General Objective

Improvement in compliance with physical activity at 10 months follow-up, taking METs-minutes/week as the unit of measurement.

## Secondary Objectives

Verify the improvement of the following parameters after the intervention:

A. Stress test:

● Demonstrate increase in VO2max.

● Demonstrate increase in exertion time.

● Demonstrate increase in workload.

● Decrease the presence of symptoms.

B. Analytical:

● Obtain improvement in lipid profile.

● Decrease in CRPus.

C. Lifestyle:

● Demonstrate increased adherence to Mediterranean diet.

● Demonstrate improved outcomes in psychological state.

● Demonstrate increased willingness to quit smoking and smoking cessation.

● Demonstrate a decrease in the sedentary lifestyle indicator.

● Demonstrate an earlier return to work.

D. Arterial stiffness

Improving carotid-femoral pulse wave velocity measurement

E. Socio-economic variables

To evaluate the cost per patient/month in the control cases of conventional rehabilitation and extended tele-rehabilitation intervention.

# Sources of Information and Scope

The information sources for the present study are:

● Participating investigators.

● Data from the patient's medical history.

● Quality of life questionnaires (EQ-5D), Adherence to Mediterranean diet, physical activity (IPAQ), anxiety-depression questionnaire (HAD).

● Analytical data.

● Pulse wave velocity.

● Data derived from stress tests (treadmill).

● Socio-occupational data

The two rehabilitation protocols that are compared are those that have been adopted in each hospital centre. At La Fe hospital it has been in operation for years and at the Arnau de Vilanova hospital it is to be initiated with the present study. There are no additional tests except for the completion of the questionnaires mentioned above.

All necessary data will be collected in a data collection logbook (DCL).

Patients will be recruited from the Cardiology ward, in both hospitals.

# Study Design

## Type of Study

Phase III clinical trial, feasibility, controlled and randomised, with two branches (intervention group by cardiac telerehabilitation and conventional rehabilitation control group in the hospital), developed in the cardiology service of the Hospital Arnau de Vilanova and Hospital Universitari i Politècnic La Fe.

The trial will be randomised, as the inclusion of each patient will be randomised by a unit external to the researchers, which will establish to which group the patient will be assigned. However, the characteristics of the interventions do not allow the study to be blinded either for the patient or for the professional. However, the analyses, stress tests and shuttle tests will be performed in a masked manner without the assigned group being identifiable by the investigators carrying out the examinations.

Sixty patients after acute coronary syndrome from two hospitals will be included.

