o Calories. METs, distance, speed, GPS position

o Exercise quality index (% of target achievement).

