**C. Pulse Wave Velocity (PWV)**

Carotid-femoral PWV is determined by ultrasound using an iE33 (Philips Medical Systems, USA), with an S 113 transducer (7-10 MHz). First, the time between the R wave of the ECG and the onset of the systolic Doppler wave in the right common carotid artery is measured. Subsequently, the time between the ECG R-wave and the foot of the systolic Doppler wave in the radial and femoral artery is measured. For each measurement, 6 cardiac cycles are averaged. The distance between measurement points, marked on the skin, is measured with a specially designed compass avoiding variability attributed to body contour. The PWV is calculated as the distance between the measurement points divided by the carotid-femoral or carotid-radial time difference (transit time of the pulse wave between the two points), in metres per second. Subjects remain at rest in a quiet, temperature-controlled room 10 minutes prior to measurements, which will be performed in the morning and according to published procedures 6. All measurements will be performed by the same scout.

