## Variables

1. Principal Variable

Since the main objective is adherence to a physical activity program, the main variable of the study is the METS-minute/week measure. Obtained from the IPAQ questionnaire.

1. Secondary variables

1. Clinical data: age, sex, STEMI, NSTEMI, unstable angina, stable angina, number of vessels, number of stents, complete revascularisation, active smoking, former smoker, hypertension, dyslipidaemia, diabetes mellitus, left ventricular ejection fraction, beta-blockers, ACE inhibitors/ARBs, statins, dual antiplatelet therapy.

2. Socio-occupational data: active worker, days until return to work after discharge.

3. Physical examination: systolic blood pressure, diastolic blood pressure, heart rate, body mass index (BMI), waist circumference, hip circumference.

4. Exercise test: VO2max, exercise time, maximal heart rate, maximal blood pressure, recovery time, ST decline, angor.

5. Pulse wave velocity.

6. Analytical data: glucose, creatinine, total cholesterol, LDL cholesterol, HDL cholesterol, triglycerides, CRPus, HbA1c.

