## Economic evaluation: cost-effectiveness analysis

The study includes a cost-effectiveness analysis to assess the costs and impact on health-related quality of life of the telerehabilitation intervention compared to in-hospital rehabilitation and the control group. The cost analysis will be carried out from the funder's perspective, including direct health care costs (pathology-related emergency visits, hospitalisations for the same cause, diagnostic and therapeutic tests such as revascularisations...) during follow-up. It will also include the costs derived from the intervention, which in the case of conventional rehabilitation, the programd schedule includes 16 rehabilitation visits, 8 rehabilitation sessions (with a physiotherapist, a nurse and a nursing assistant per session) and 8 educational talks. In the telerehabilitation group, the schedule includes 4 rehabilitation visits, 3 sessions (with a physiotherapist and a nurse) and 4 educational sessions. Unscheduled visits and sessions during the follow-up will also be included. The unit costs will be obtained from the Generalitat Valenciana catalogue.

Additionally, an analysis will be performed from a social perspective, including also indirect health care costs due to lost productivity of the patient (number of sick leaves and time to return to work after the event). Indirect costs will be reported by the patient in the follow-up data collection logbook. Effectiveness will be assessed by the physical activity performed by the patient, reported by the patient at the end of the follow-up, measured in METs-minutes/week.

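### The list of masked examinations leaves out pulse wave velocity and does not protect collection of the self-reported primary outcome, yet it includes shuttle tests that are defined nowhere else

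*Protocol*

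**What the plan says.** Section 6.1 states that "the characteristics of the interventions do not allow the study to be blinded either for the patient or for the professional". It then names what is masked: "the analyses, stress tests and shuttle tests will be performed in a masked manner", with the arm hidden from those who carry out the examinations. No other section adds to that list.

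Section 7.3 (Variables) says that "the main variable of the study is the METS-minute/week measure. Obtained from the IPAQ questionnaire". Section 9.4 (Economic evaluation) confirms that this is the patient's own account: "Effectiveness will be assessed by the physical activity performed by the patient, reported by the patient at the end of the follow-up". The questionnaire in section 7.2 asks for recalled days and minutes. It is scored with fixed weights: 3.3 METs for walking, 4 for moderate and 8 for vigorous activity.

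Section 4.2 lists carotid-femoral PWV as a secondary objective. Section 7.2 C describes Doppler timing against the ECG, a skin distance taken with a compass, and averaging over 6 cycles. It adds: "All measurements will be performed by the same scout". It does not mention allocation.

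**The concern.** Where patients and therapists must know the arm, the remaining protection lies in who measures, what they know, and when. The protocol uses that protection for the stress test but not for PWV, where masking is just as feasible and the operator's judgement enters the result. For the primary variable the patient cannot be masked, but the circumstances of collection can be controlled, and the protocol does not control them. One of the three masked items cannot be matched to any defined measurement, so the list cannot be followed with certainty.

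Two things are at stake. The PWV comparison could be moved by an operator who knows the arm. The primary comparison could take on a difference created by how the questionnaire is handed out or checked, on top of whatever unblinded patients bring to it themselves.

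**Working it through.** **Step 1. Set the masked list beside the measurements.**

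| Item | Where it appears | On the masked list? |
| --- | --- | --- |
| Laboratory analyses | 4.2, 6.5, 6.6, 7.2 A, 7.3, Annex 1 | Yes, if this is what analyses means |
| Stress test | 4.2, 6.5, 6.6, 7.3, Annex 1 | Yes |
| Shuttle tests | 6.1 only | Yes |
| Carotid-femoral PWV | 4.2, 6.5, 6.6, 7.2 C, 7.3, Annex 1 | No |
| IPAQ (primary) | 6.5, 7.2 B, 7.3, Annex 1 | No |
| HAD, EQ-5D, Mediterranean diet | 6.5, 7.2 B, Annex 1 | No |

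If analyses meant the statistical analysis, that would still not protect data collection.

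**Step 2. PWV.** PWV is distance divided by transit-time difference. A given percentage error in the compass distance is therefore the same percentage error in PWV, and the choice of the wave onset sets the denominator. Using one operator removes between-operator variation. It does not conceal allocation.

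**Step 3. IPAQ.** No section says who hands out, checks or scores the questionnaire. The first telerehabilitation session in section 6.4 reserves 60 minutes for data collection, without saying which data or who collects them. The items allow a don't-know answer, and Annex 1 records only one number. Timing also differs: section 6.5 lists the surveys at 4 months, while section 6.6 and Annex 1 have them only at the start and at 10 months.

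**Step 4. The protocol's own figure.** Section 9.1 gives 27 per arm, two-sided alpha 0.05, means of 5000 and 4000, and 95% power. It gives no SD.

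- Standard error = SD × √(2/27) = 0.2722 × SD, with 52 degrees of freedom.
- Solving for 95% power gives SD ≈ 1000 by the noncentral t, or about 1019 by the normal approximation.
- At SD 1000 the noncentrality is 1000/272.2 = 3.67, and power is 0.950 (t) or 0.957 (normal).

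The stated 95% therefore fits an unstated SD of about 1000.

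**Step 5. Sensitivity to a between-arm shift in the recorded IPAQ, with no true effect.** The shifts and SDs are assumptions.

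- 10 minutes of walking a day: 3.3 × 10 × 7 = 231 METs-minutes/week.
- SD 1000: 231/272.2 = 0.85, rejection rate 13%; a shift of 500 gives 500/272.2 = 1.84, rejection rate 44%.
- SD 2000 (standard error 544.3): 231/544.3 = 0.42, rejection rate 7%; 500/544.3 = 0.92, rejection rate 15%.
- Whole assumed difference: 1000/3.3 = 303 minutes of walking a week, or about 43 minutes a day.

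These rates hold whatever the source of the shift. They do not separate staff influence from patient recall.

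**The case against.** The strongest reply is that the primary variable is the patient's own recall, so no assessor mask can reach it, and section 6.1 openly says that patients are unblinded. Scoring is fixed arithmetic with little room for discretion. No section says that programme staff administer the IPAQ or that the PWV operator knows the arm. PWV also has safeguards: averaged cycles, standard conditions, a purpose-made compass and a single operator.

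Much of this stands. Masked scoring cannot remove over-reporting, which is inherent and disclosed. What remains is that the protocol enumerates what is masked, PWV is not included, and no rule keeps IPAQ collection away from programme staff.

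A reader might go further, but the documents do not support these inferences:

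- *Over-reporting in the telerehabilitation arm could explain the whole effect.* The arithmetic is possible (4000 × 1.25 = 5000), but only a difference between arms matters, and nothing shows its size or direction. Control patients also have 16 hospital visits, eight of them for exercise, and a talk on physical exercise. The sensor data in the other arm ("Calories. METs, distance, speed, GPS position") could make recall more accurate rather than less.
- *The masked exercise measures play no part in the conclusions.* VO2max and exercise time are secondary outcomes, collected at baseline and 10 months and compared between groups. They measure capacity, which is not the same as activity.
- *PWV and the IPAQ are the endpoints most open to bias.* HAD, EQ-5D and the diet score are also unmasked self-reports, at least as exposed as PWV.
- *Shuttle tests is a leftover term.* Section 6.6 has an otherwise undefined row for physical working capacity, which may be the same test.

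**Conclusion.** The point holds as a gap in the stated masking. PWV is operator-dependent, a named objective and feasible to mask, but it is left out. Collection of the primary questionnaire has no safeguard. One masked item is undefined. This should be corrected, although it does not invalidate the design.

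The size of any bias cannot be estimated from the documents. The rejection rates of 13% and 7% for a 231-unit shift show only how sensitive the comparison is. They rest on assumed shifts and on an SD the protocol does not state. No comparable figure can be given for PWV, because the protocol states neither an expected value nor a spread.

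**What to change.** 1. In section 6.1, add carotid-femoral PWV to the masked examinations. Keep the single operator, who receives only the patient code.
2. In section 6.5, state that the patient completes the IPAQ alone, before contact with programme staff, at each visit where it is collected. Have it scored with the section 7.2 formula from the patient code alone. The stress-test investigator should not be given this task: no stress test takes place at 4 months, and discussing daily activity with the patient could break that investigator's mask.
3. Clarify what shuttle tests are, and whether they are the physical working capacity row in section 6.6. Do not simply delete the term.
4. Describe the primary result as self-reported physical activity and report it beside the masked exercise-test results. It should not be made conditional on them: if fitness truly did not differ, agreement in sign on one measure would be about a coin flip.

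The cost is a small change in visit order and keeping the PWV operator out of programme delivery. No new tests are needed. Patients may still reveal their arm, so the mask will be imperfect, and over-reporting should be stated as a remaining limitation.
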